#### **Funding**

Funding through the German Center for Diabetes Research (DZD) e.V.

## **1. Background**

### **Pathogenesis of type 2 diabetes mellitus**

Type 2 diabetes mellitus is a disease with a significant and increasing prevalence (age of 50-80 years: 5-18%) and is associated with serious macro- and microangiopathic complications. The heterogeneous clinical picture of type 2 diabetes mellitus is caused by genetic and environmental factors [1].

Two important mechanisms play a role in the pathogenesis: on the one hand, the insulin resistance of the target tissue and, on the other hand, a secretion defect of the  $\beta$ -cells of the islet organ of the pancreas [2–4].

One of the main effects of insulin in target tissues is to control the uptake of glucose into cells. The liver, skeletal muscles and adipose tissue are considered to be insulin-sensitive target tissues. Insulin resistance of these tissues is considered to be one of the main defects in the development of type 2 diabetes mellitus. To quantify insulin sensitivity or resistance, the effect of insulin on glucose uptake is usually measured in a hyperinsulinemic-euglycemic clamp [5].

### **Insulin action in the CNS**

The uptake of glucose into neurons occurs via an insulin-independent mechanism, so that the CNS does not depend on the presence of insulin for glucose metabolism. Nevertheless, insulin receptors are present in the CNS [6]. The specific insulin action in the CNS became the focus of research when the insulin receptor in animals was selectively knocked out in the brain: the test animals consumed much more food than controls, became overweight and developed insulin resistance throughout the body [7]. In further experiments, various functions of central insulin action in animals were discovered. Insulin action in the brain influences e.g. food intake, energy expenditure, systemic lipolysis, systemic glucose metabolism, systemic insulin sensitivity and insulin secretion from the beta cells [8].

In humans, we and others have also been able to show that insulin has an effect in the brain:

### **Own results in this area**

Using magnetoencephalography (MEG), we were able to demonstrate insulin effects on the cerebral cortex in humans. The insulin effects we have detected are clearly correlated with the weight of the people examined [9]. In addition, the effect of central nervous insulin

decreases with increased saturated free fatty acids in the plasma [10] and with increasing age [11]. Impaired transport across the blood-brain barrier also seems to play a pathogenetic role in brain insulin resistance [12].

The intranasal administration of insulin allows insulin to be transported selectively to the human brain, bypassing the blood-brain barrier [13, 14]. Using this method, we were able to show that nasal insulin primarily affects the neuronal response to visual food stimuli [15]. We were also able to show that nasal insulin has no effect on global cerebral blood flow [16]. Even after nasal insulin application, the higher the weight, the lower the insulin effect [17, 18]. Thus, we were able to confirm results obtained with intravenous insulin with intranasal insulin.

To date, there have only been a few experimental studies in humans on the question of how insulin action in the brain affects peripheral metabolism. In cooperation with colleagues in Lübeck and New York, we were able to show that intranasal administration of insulin systemically suppresses lipolysis [19]. In a further study, there were initial indications that regulation of peripheral insulin sensitivity through insulin action in the central nervous system is also possible in humans, as shown in laboratory animals [20]. We examined this indirect result in more detail in another study. We measured peripheral insulin sensitivity in healthy men using the hyperinsulinemic-euglycemic clamp. During the clamp we applied 160 U insulin or placebo intranasally. While insulin sensitivity did not change after placebo spray, there was a significant improvement in peripheral insulin sensitivity after insulin nasal spray.

Whether these results can also be transferred to women cannot be answered with the previous experiment. The group of Hallschmid et al. [21] was able to show that there are gender-specific differences in the response to intranasal insulin. In this study, men and women applied intranasal insulin for 8 weeks. The men showed a reduction in weight, which was not present in the women. The female sex hormones thus appear to have an influence on cerebral insulin action. Since the female sex hormones are subject to cycle-related fluctuations and it has long been suspected that this affects insulin sensitivity, women without hormonal contraception should be examined in the first and second half of the cycle.

For this purpose, the now planned study is to be carried out.

## 2. Research question

We hypothesize insulin action in the central nervous improves peripheral insulin sensitivity in women and that this improvement correlates with changes in autonomic and central nervous system activity. In addition, it should be investigated whether there are cycle-dependent differences.

## 3. Study population

A total of 10 subjects (normal weight, BMI up to 24 kg/m^2, no hormonal contraceptives) will be included. In previous studies with nasal insulin, there were clear sex differences. In order to be able to compare the collected data with existing data from men [22], similar inclusion criteria should be used. In addition, peripheral insulin sensitivity is significantly influenced by the menstrual cycle [23]. We will therefore examine the subjects in the first and second half of the cycle. The study participants are recruited by specifically addressing suitable participants and by advertising via circular mails and notices.

### Inclusion Criteria:

female adult volunteers

HbA1c <6.0%

Age between 18 and 30 years

Standard routine laboratory

No underlying diseases

No medication intake

No hormonal contraception

Understanding of declaration of consent, study explanations and instructions

### Exclusion criteria

- People who have non-removable metal parts in or on their body, such as:

pacemaker

artificial heart valves

metal prostheses

implanted magnetic metal parts (screws, plates from surgeries)

coil

Metal shards/shrapnel

fixed braces

Retainers go over more than four teeth

acupuncture needle

insulin pump

intraport

tattoos, eye shadow etc.

- People with reduced temperature sensitivity and/or increased sensitivity towards warming of the body
- Cardiovascular disease cannot be ruled out, such as manifest coronary heart disease, heart failure greater than NYHA 2, previous heart attack, condition after a stroke
- People with a hearing disorder or an increased sensitivity to loud noises
- Persons with claustrophobia (claustrophobia)
- Subjects who are minors or who are unable to consent are also excluded
- Pregnancy or lactation
- Subjects who had an operation less than 3 months ago
- Concurrent participation in other interventional studies
- Acute illness or infection within the last 4 weeks
- Neurological and psychiatric disorders
- Subjects with hemoglobin values  $Hb < 12g/dl$  (at screening)
- Allergic diseases
- Individuals with a history of heparin-induced thrombocytopenia (HIT).

Subjects must be in good general condition with no serious underlying diseases assessed during the clinical examination by the investigator. If there are doubts about these requirements, further laboratory values may be determined after a clinical examination.

#### **4. Sample size calculation**

In the previous study [22], the glucose infusion rate in lean men was influenced by insulin nasal spray during the clamp. The effect size was (Cohen's)  $d_z = 1.178$ . Based on this information we calculated the sample size ( $\alpha = 0.05$ , power (1-beta error probability) = 0.9). A sample size of  $n = 10$  is required. If there are drop-outs, these subjects are replaced by new ones who have to go through the experiment from the beginning.

## 5. Study course and research methods

At least one day before the start of the study, the participants will be informed about the study. Participants can only take part in the study after they have given their written consent. At the first appointment (metabolic characterization, precise examination of exclusion criteria), the subjects are clinically examined after anamnesis, including determination of laboratory values such as blood count, inflammation values, electrolytes, kidney values, liver values, lipids, coagulation, HbA1c, hormones, urine tests and anthropometric measurements. In addition, a detailed cycle anamnesis takes place. In addition, DNA for genotyping for metabolically relevant polymorphisms is optionally preserved with the separate consent of the subjects (project number genetic biobank 175/2017BO1).

The participants will be examined on two independent days in the first and second half of the cycle using a hyperinsulinemic euglycemic clamp and functional magnetic resonance imaging (fMRI), once with nasal insulin administration, once with nasal placebo administration. The order of investigations (nasal insulin, nasal placebo) is randomized and blinded, the interval between trials will be 2 days to 8 weeks.

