### **Functional MRI measurement**

The participants will be subjected to fMRI measurement and behavioral tests on two independent days (first and second half of the cycle). Measurements will start at 8 a.m. on both days for all subjects in order to rule out circadian fluctuations. Intranasal insulin is administered on both examination days.

The neurophysiological measurements on the MRI scanner are made up of two measurement blocks each. The first part always takes place basally, with the second being carried out after the intranasal administration of insulin. The breaks between the measurements are used to fill out questionnaires on eating behavior and mood. The fMRI measurements each last about 40 minutes, with the test persons having no task during the measurements in the basal measurement. An ECG is recorded during the MRI measurement.

During the first MRI measurement, an anatomical image of the brain is taken and a measurement is performed to quantitatively record the proton density (quantitative water content imaging). During the first and second fMRI measurement, the brain activity is measured at rest. The absolute cerebral blood flow (CBF) enables brain activity to be recorded in physiologically defined and thus comparable units (ml/100g/min) without stimulation. To capture coherent patterns of spontaneous blood oxygen level dependent (BOLD) fluctuations in the resting state, a standard fMRI BOLD sequence is performed directly after the CBF measurements. Furthermore, at the first and second measurement, a spectroscopic examination (1H-MRS) of the gray and white matter is recorded to detect metabolites that are modulated by inflammatory processes and intranasal insulin. Only in the second part of the fMRI measurement, subjects are asked to look at the food images and to press a button when a cross appears. This ensures their attention.

The examinations at the MRI are carried out by people with magnetic resonance imaging certification, at least 2 people are on site for each measurement. The examiners have extensive experience with the examination methods to be used.

Between the fMRI measurements, the participant's subjective condition is checked using a visual analogue scale (eating, drinking, etc.). Mood is recorded using the German form of the positive and negative affect schedule (PANAS) [24]. Other questionnaires on eating behavior

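### The protocol does not settle whether each woman has two clamp days or four; with two, cycle-dependence of the spray effect rests on a 5-versus-5 comparison between women

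*Protocol*

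**What the plan says.** The clamp schedule is in Protocol section 5, in the introductory text on study course: "The participants will be examined on two independent days in the first and second half of the cycle using a hyperinsulinemic euglycemic clamp" and fMRI, "once with nasal insulin administration, once with nasal placebo administration". The spray order is randomized and blinded, and trials are 2 days to 8 weeks apart. No visit count is given, and balance of spray over cycle half is not mentioned.

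The fMRI subsection uses closely similar wording for what is plainly one day per half: "behavioral tests on two independent days (first and second half of the cycle". It gives intranasal insulin on both of those days.

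Cycle phase is part of the research question. Section 2 says "it should be investigated whether there are cycle-dependent differences", and section 3 states that "peripheral insulin sensitivity is significantly influenced by the menstrual cycle". The end of the background section gives the same reason for examining women in both halves.

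Section 4 sizes a single paired insulin-versus-placebo comparison, with Cohen's dz = 1.178 from lean men, alpha 0.05 and "power (1-beta error probability) = 0.9". This gives 10 women, and drop-outs are replaced.

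**The concern.** The two readings are different experiments. With an insulin day and a placebo day in each half, every woman shows the spray effect twice, and the effects in the two halves can be compared within her. With one day per half, no woman receives both sprays in the same half. Her insulin-minus-placebo difference then contains the difference between cycle halves, which the protocol itself expects to be real.

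Two things are at stake under the two-day reading. The main comparison depends on how evenly the sprays fall over the halves and on whether phase is in the model, and the text secures neither. The cycle-dependence of the spray effect on clamp insulin sensitivity loses its within-woman contrast, and no later analysis can recover contrasts that were not observed.

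**Working it through.** **Inputs.** From section 4: dz = 1.178, alpha = 0.05, target power 0.9, n = 10. Sidedness is not stated; two-sided is used because it reproduces n = 10. The sizes of the phase effect, the interaction and the between-woman variance share are assumptions, because the protocol gives none. All powers use the noncentral t distribution, with the SD of the paired difference set to 1.

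**1. The plan's own figure.** Paired t-test, noncentrality 1.178·√n, n−1 df. Power is 0.870 at n = 9 and 0.911 at n = 10, so n = 10 is correct for the single paired comparison.

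**2. What two days estimate.** Let t_F and t_L be the spray effects, and m_F and m_L the placebo levels, in the first and second half. The insulin-minus-placebo difference is:
- insulin in the first half: D_A = t_F + (m_F − m_L)
- insulin in the second half: D_B = t_L − (m_F − m_L)

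Their average is (t_F + t_L)/2, so the phase term cancels. Their contrast is (t_F − t_L) + 2(m_F − m_L), which mixes the interaction with twice the plain phase effect.

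Design-matrix ranks agree:
- woman + treatment + half, both patterns present: 12 of 12
- the same model, all women on one pattern: 11 of 12
- adding treatment × half, two days: 12 of 13
- adding treatment × half, four days: 13 of 13

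**3. Main effect adjusted for phase, two days.** The variance is (1/n_A + 1/n_B)/4, with 8 df.
- 5:5: variance 0.1000, noncentrality 3.725, power 0.902
- 7:3: variance 0.1190, noncentrality 3.414, power 0.847
- 8:2: variance 0.1563, noncentrality 2.980, power about 0.74

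If all women start in the same half, simple randomization gives 8:2 or worse with probability 2·(1 + 10 + 45)/1024 = 0.11, and a single pattern for all ten with probability 2/1024 = 0.002. At 8:2 an unadjusted mean difference carries (8 − 2)/10 = 60% of the phase difference as bias.

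**4. Main effect without adjustment.** The phase term of each woman's difference stays in the error. For an assumed phase effect of 0.5 SD, dz = 1.178/√(1 + 0.5²) = 1.054 and power is 0.84. For an assumed 1 SD, dz = 1.178/√2 = 0.833 and power is 0.65. These figures hold only for an unadjusted paired test under those assumptions.

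**5. Spray-by-half comparison.** Take the extreme case: an effect of 1.178 SD in one half and none in the other.
- Two days, D_A against D_B, 5 versus 5, with the phase term assumed zero or removed by baseline: noncentrality 1.178/√(2/5) = 1.863, 8 df, power 0.37.
- Two days without that assumption: each woman's sum over her two days is compared between groups. That contrast is free of the phase term but carries between-woman variance. If that share of the variance is 0, 0.5, 0.7 or 0.8, power is 0.37, 0.16, 0.11 or 0.09.
- Four days, within woman, equal uncorrelated variance on all days: dz = 1.178/√2 = 0.833, n = 10, 9 df, power 0.65.

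**The case against.** The strongest reply is that the sentence can mean a pair of days in each half. The fMRI subsection puts the cycle halves in brackets after the days and section 5 does not, and a minimum gap of two days suits a pair within one half. If four days are meant, the problem disappears. This stands as a possible reading, but nothing in the protocol confirms it.

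A reader might infer that the two-day design confounds the insulin effect with cycle phase for the trial as a whole. It does not. Spray order is randomized, the phase term cancels over the two patterns, and with phase in the model at 5:5 the loss is from 0.911 to 0.902. The confounding is within each woman; at group level it is the interaction that falls between women.

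A reader might also infer that the cycle question cannot be answered. That is too strong. Insulin sensitivity is calculated before the spray on each clamp day, so its difference between halves is seen within woman (though mixed with visit order if all women start in the same half). The fMRI subsection also gives a pre-spray scan and an insulin scan in each half. What is lost is the within-woman comparison of the spray effect on the clamp index. Even four days reach only 0.65 in the extreme case, so that question is underpowered either way.

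The number of visits and the allocation of sprays to cycle halves are design content, so an analysis plan could not settle them afterwards.

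**Conclusion.** The concern holds in this form: the protocol leaves the number of clamp days per cycle half open, and its most direct reading is the weaker design. Under that reading the main comparison keeps power 0.90 if sprays are balanced 5:5 over the halves and phase is modelled, and falls to 0.85 at 7:3 and 0.74 at 8:2. The spray-by-half comparison has power of at most about 0.37 for the largest interaction considered, and less if between-woman variance enters.

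These figures assume two-sided testing, an additive phase effect for the main comparison, and the same SD of the paired difference in women as lies behind dz = 1.178. The sample size of 10 is not in error for the one comparison it was computed for.

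There is a linked inconsistency. Section 5 describes the clamp and fMRI examinations together as once with insulin and once with placebo, while the fMRI subsection has insulin on both days. These statements must be reconciled.

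**What to change.** State in section 5 how many clamp days each woman has in each cycle half, and to which pair of days the 2-day-to-8-week interval applies.

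- If four are intended: say that both sprays are given in each half, with order randomized within the half. This costs one sentence.
- If two are intended: balance spray over cycle half in the randomization (5:5), and let a replacement for a drop-out take the pattern of the woman replaced. Include cycle half in the analysis of the insulin effect, use the same-day pre-spray index as baseline, and label the spray-by-half comparison exploratory. This costs a blocked randomization list, one model term and a narrower claim. It adds no visits.

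In the same edit, reconcile the two descriptions of which spray is given on the fMRI days. Moving from two clamp days to four, if four are not already planned, would add procedures for every woman and is not needed to protect the main comparison.

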### Euglycemic hyperinsulinemic clamp

The investigation is carried out after an overnight fasting period in a lying position. A venous access is placed in an elbow vein for the infusion of glucose (10%) and insulin. Another venous access is placed in a vein on the back of the hand. This hand is warmed with the help of heating pads (up to a maximum of 40°C), which allows the collection of arterialized venous blood (continuous determination of glucose, further blood collection [labelled glucose, insulin, C-peptide, free fatty acids, nitroso-glutathione, as well as blood for preservation for later investigations of other hormones and metabolites]).

After taking the first blood samples, the continuous infusion of [6,6-H2] glucose is started. This starts with a bolus of 3.6 mg/kg followed by a continuous infusion of 0.036 mg/kg/min. After 2 hours, an insulin infusion (human insulin in 0.9% NaCl solution) is started. After an insulin bolus, 0.25 mU/kg/min of insulin is infused continuously for 210 minutes. During the entire duration of the insulin infusion, the blood sugar is measured every 5 - 10 min and kept in the normal range by means of a variably infused 20% glucose solution with labeled [6,6-H2] glucose. Before and twice after nasal insulin/placebo administration at minute 90 of the

clamp, insulin sensitivity is calculated as an index from measured insulin levels and glucose infusion rate. Endogenous glucose production (EGP) will be calculated for the same time periods using Steele's equation. From these calculations, the insulin sensitivity of the liver, muscles and other tissues can be estimated. The respective blood samples are given in the following overview. The total volume of blood samples is approximately 130 ml per test.

In the experiment, insulin levels in the central nervous system will be increased 90 minutes after the onset of the hyperinsulinemic euglycemic clamp via an intranasal administration. For this purpose, human insulin is used in the form of an intranasal spray (16 strokes of 10 U), with a corresponding amount of placebo being used in the placebo test. On the placebo days, the *iv* insulin infusion was slightly increased for 20 minutes after administration of the nasal spray in order to simulate spill-over effects from the insulin days.

During the times when insulin sensitivity is calculated, we will record an ECG for about 10 minutes to record heart rate variability as a measure of the activity of the autonomic nervous system.

[figure not shown]

Abb. 1. Test procedure: Clamp

### **Functional MRI measurement**

The participants will be subjected to fMRI measurement and behavioral tests on two independent days (first and second half of the cycle). Measurements will start at 8 a.m. on both days for all subjects in order to rule out circadian fluctuations. Intranasal insulin is administered on both examination days.

The neurophysiological measurements on the MRI scanner are made up of two measurement blocks each. The first part always takes place basally, with the second being carried out after the intranasal administration of insulin. The breaks between the measurements are used to fill out questionnaires on eating behavior and mood. The fMRI measurements each last about 40 minutes, with the test persons having no task during the measurements in the basal measurement. An ECG is recorded during the MRI measurement.

During the first MRI measurement, an anatomical image of the brain is taken and a measurement is performed to quantitatively record the proton density (quantitative water content imaging). During the first and second fMRI measurement, the brain activity is measured at rest. The absolute cerebral blood flow (CBF) enables brain activity to be recorded in physiologically defined and thus comparable units (ml/100g/min) without stimulation. To capture coherent patterns of spontaneous blood oxygen level dependent (BOLD) fluctuations in the resting state, a standard fMRI BOLD sequence is performed directly after the CBF measurements. Furthermore, at the first and second measurement, a spectroscopic examination (1H-MRS) of the gray and white matter is recorded to detect metabolites that are modulated by inflammatory processes and intranasal insulin. Only in the second part of the fMRI measurement, subjects are asked to look at the food images and to press a button when a cross appears. This ensures their attention.

The examinations at the MRI are carried out by people with magnetic resonance imaging certification, at least 2 people are on site for each measurement. The examiners have extensive experience with the examination methods to be used.

Between the fMRI measurements, the participant's subjective condition is checked using a visual analogue scale (eating, drinking, etc.). Mood is recorded using the German form of the positive and negative affect schedule (PANAS) [24]. Other questionnaires on eating behavior

include the Questionnaire on Eating Behavior [25] and the German version of the Food Cravings Questionnaire [26]. Depression is recorded using the Beck Depression Inventory (BDI-II) [27].

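### The protocol contradicts itself on whether the MRI visits have a placebo condition; if the fMRI section governs, no insulin effect on the brain or behavioural measures can be isolated

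*Protocol*

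**What the plan says.** The overview paragraph of protocol section 5 has participants examined in both halves of the cycle by clamp and by "functional magnetic resonance imaging (fMRI), once with nasal insulin administration, once with nasal placebo administration". It adds: "The order of investigations (nasal insulin, nasal placebo) is randomized and blinded".

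The subsection on functional MRI describes "fMRI measurement and behavioral tests on two independent days (first and second half of the cycle"), and then states "Intranasal insulin is administered on both examination days". Within a day the order of the two blocks is fixed: "The first part always takes place basally, with the second being carried out after the intranasal administration of insulin". Cerebral blood flow (CBF), resting BOLD and spectroscopy are taken in both blocks. The picture task is not: "Only in the second part of the fMRI measurement, subjects are asked to look at the food images". The behavioural tests (picture recall, attention, verbal memory, reward learning) follow the second block.

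Placebo spray is described for the clamp but is not mentioned in the fMRI or behavioural text. The research question in section 2 is that insulin acting in the brain improves peripheral insulin sensitivity and that "this improvement correlates with changes in autonomic and central nervous system activity"; it also asks about differences across the cycle.

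**The concern.** The two texts prescribe different experiments. Under the overview, the MRI measures have a randomized, blinded placebo comparator. Under the fMRI subsection they are a single-condition, before-and-after study repeated in each cycle half. Which spray is given at which visit, and whether it is randomized and blinded, is protocol content and not something to be left to an analysis plan.

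The choice decides what the trial can say about the central nervous part of its hypothesis. A basal-to-post change without placebo also contains whatever happens with time in the session, a second scan and the spray procedure. A measure taken only after insulin contains no insulin contrast at all. The section on expected benefit promises to learn which brain centres are involved, and that promise rests on these data.

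**Working it through.** **1. The protocol's own figure.** Section 4 gives d_z = 1.178, alpha 0.05, power 0.9 and n = 10. For a paired t-test with n − 1 degrees of freedom and noncentrality d_z·√n:
- n = 9: 1.178 × 3 = 3.534, two-sided power 0.870.
- n = 10: 1.178 × 3.162 = 3.725, two-sided power 0.911.

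So n = 10 reproduces with a two-sided test. The figure concerns the glucose infusion rate in the clamp and says nothing about the MRI.

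**2. What each text allows to be estimated.** Write each measurement as intercept + cycle half + second block + insulin, coding each term 0 or 1.

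*fMRI subsection, resting measures:*

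| Day | Block | Intercept | Cycle half | Second block | Insulin |
|---|---|---|---|---|---|
| first half | basal | 1 | 0 | 0 | 0 |
| first half | post | 1 | 0 | 1 | 1 |
| second half | basal | 1 | 1 | 0 | 0 |
| second half | post | 1 | 1 | 1 | 1 |

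The last two columns are identical, so the matrix has rank 3 for 4 parameters. Insulin and second block are the same variable, and no analysis can separate them.

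*fMRI subsection, post-only measures:* the rows (intercept, cycle half, insulin) are (1, 0, 1) and (1, 1, 1). The rank is 2 for 3 parameters, because insulin is always present.

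*Overview, two MRI days in total, with some women receiving insulin in the first half and others in the second:* the rank is 4 of 4 for resting measures and 3 of 3 for post-only measures. An average insulin effect is then estimable across women. Within any one woman, however, the post-only rows are (1, 0, 1) and (1, 1, 0), or the reverse: rank 2 for 3 parameters. Her insulin-placebo difference is also her difference between cycle halves, so whether the insulin effect depends on the cycle cannot be estimated within a woman.

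**3. Size of the pre-post problem, on assumed drift.** The protocol gives no drift figure, so these values are assumptions. Suppose insulin has no effect and the mean non-insulin drift is δ, in SDs of the within-woman change. A one-sample t-test of that change at n = 10 has 9 degrees of freedom, critical value 2.262 and noncentrality δ·√10:

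| Assumed δ | δ·√10 | Probability of a significant result |
|---|---|---|
| 0.2 | 0.632 | 0.088 |
| 0.25 | 0.791 | 0.109 |
| 0.5 | 1.581 | 0.293 |
| 0.8 | 2.530 | 0.616 |

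The nominal rate is 0.05. The aliasing in step 2 does not depend on these values.

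**4. The correlation hypothesis.** Adding the same constant to every woman's brain change leaves its correlation with the clamp effect unchanged: corr(X + c, Y) = corr(X, Y). Only drift that varies between women can alter it. The probabilities in step 3 therefore concern a claim about mean change, not the correlation.

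**The case against.** The overview is one compressed sentence, and its insulin-and-placebo clause could have been meant for the clamp alone, where placebo is spelled out. The fMRI subsection is specific and consistent with itself, naming insulin twice. That may explain how the conflict arose, but the sentence attaches the placebo to both procedures. If only the clamp was meant, the overview is the text to correct.

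The opposite reading is also open. The placebo section wants the two conditions to be indistinguishable to participants and does not limit this to the clamp. A reader might infer from the fMRI subsection that the trial certainly cannot isolate any insulin effect on the brain. The documents do not support that as a fact, because it holds only if that subsection governs.

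Three further limits stand:
- A reader might add task to the confounders of every MRI measure. CBF, resting BOLD and spectroscopy are compared at rest, so task bears only on the food-image block and the behavioural tests.
- A reader might conclude that the brain-clamp correlation is necessarily biased. A drift shared by all women would not do that.
- The sample size rests on the clamp endpoint, whose placebo control is clear, and a comparison of the two cycle halves under insulin would address part of the research question.

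These points narrow the concern. They do not remove the contradiction.

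**Conclusion.** The contradiction is real and has to be resolved; what follows from it depends on which text governs.

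- **fMRI subsection governs.** Insulin is fully aliased with block order for the resting measures, and the post-only measures have no comparator. What remains is first half versus second half under insulin. Reading this as cycle-dependent insulin action assumes similar time and spray effects in both halves.
- **Overview governs, two MRI days in total.** A placebo contrast exists across women, but spray and cycle half are confounded within each woman.

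The false-positive probabilities of 0.11 and 0.29 illustrate assumed drifts of 0.25 and 0.5 SD, for a pre-post test of the mean that the protocol does not itself specify. The placebo-controlled clamp result, on which n = 10 was calculated, is not touched.

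**What to change.** Reconcile the section 5 overview with the fMRI subsection, stating the number of MRI days and the spray on each.

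- **If two insulin-only MRI days are run:** take fMRI out of the overview's statement on placebo, randomization and blinding. State that the MRI and behavioural data support only a comparison of the cycle halves under insulin, with the assumption of similar time and spray effects. Label the brain-clamp correlation exploratory and uncontrolled. This costs wording only, at the price of a narrower claim.
- **If placebo MRI is intended:** correct the fMRI subsection. Define the insulin effect as the insulin-minus-placebo difference in basal-to-post change for the resting measures, and as the plain insulin-minus-placebo difference for the post-only measures. Having both sprays within each cycle half means 2 × 2 = 4 MRI sessions per woman, against the two days that the fMRI subsection describes, so this may exceed what is now planned. With only two sessions, state that spray and cycle half are confounded within each woman.
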